# “One-step” approach versus “Step-up” approach minimally invasive treatment for infected pancreatic necrosis: a study protocol for a single-center, prospective, randomized controlled trial

**DOI:** 10.1186/s12876-022-02116-0

**Published:** 2022-02-03

**Keywords:** Acute pancreatitis, Infected pancreatic necrosis, Minimally invasive treatment, Randomized controlled trial

## Abstract

**Background:**

Currently, the minimally invasive “Step-up” surgical strategy is still the main treatment for infected pancreatic necrosis (IPN). However, indiscriminate implementation of the “Step-up” strategy can lead to increased numbers of operations and prolonged hospital stay. The “Step-up” approach is not appropriate for some patients due to unavailabilty of a safe puncture path. Therefore, we developed the “One-step” surgical approach to treat IPN, which is safety. However, there is still a lack of comparison of the short and long-term efficacy between the “One-step” and “Step-up” approach. Consequently, we are conducting this clinical trial to provide a reference for IPN treatment.

**Methods:**

This is an ongoing, single-center, randomized controlled trial of patients with IPN. The total sample size required for the trial (May 2021–December 2023) is approximately 128 patients. Patients will be randomly assigned to either an experimental group (One-step) or a control group (Step-up) at a ratio of 1:1 using the block randomization method. We used the case report forms and electronic data capture systems to obtain demographic information, preoperative laboratory examination, auxiliary examination results, surgery data, postoperative recovery outcomes, and follow-up outcomes. The patients will be followed up for 2 years after surgery. The primary endpoint is a composite endpoint, consisting of mortality and severe complications. The secondary endpoints include the incidence of organ dysfunction, the number of surgical procedures, mortality (the incidence of death in hospital and deaths within 30 days of discharge), hospital stay, intensive care unit stay, hospitalization costs, perioperative inflammatory marker changes, and short-and long-term complications.

**Discussion:**

Compared with the “Step-up,” the “One-step” minimally invasive surgery can significantly reduce the number of operations, reduce the length of hospital stay and hospitalization costs without increasing the incidence of composite endpoint events, and has better short- and long-term efficacy and safety. Additionally, there was no statistically significant difference in perioperative complications and mortality between “Step-up” and “One-step”. This study will assist with the formulation of an effective and scientific “One-step” minimally invasive treatment strategy for IPN, and an understanding of this technique will facilitate clinical decision-making for IPN.

*Trial Registration* ChiCTR2100044348. Trial status: Ongoing.

## Background

Severe acute pancreatitis (SAP) is a serious abdominal disease with a poor prognosis and high mortality rate [1]. There are two mortality peaks in SAP: (1) systemic inflammatory response syndrome (SIRS) and multi-organ dysfunction (MODS) in the early stage of the disease; (2) infected pancreatic necrosis (IPN) occurs in the late stage of the disease, and its incidence in the natural course of SAP is as high as 40–70% [2]. With the advancement of fluid resuscitation and other treatments, the early mortality rate has been reduced, but the treatment of IPN is still very difficult. Approximately 35–50% of SAP deaths are related to IPN surgical intervention is often required, and the outcomes of treatment are crucial to prognosis [3]. Therefore, the treatment of SAP, especially for IPN, has always been a major issue and a research hotspot in the field of digestive diseases.

In recent years, minimally invasive pancreatic necrosis tissue debridement has become the primary treatment for IPN, and most clinicians follow the “Step-up” surgical strategy, namely percutaneous catheter drainage (PCD) is performed first, and minimally invasive or open surgery are performed successively for patients for whom infection is not controlled [4–6]. However, indiscriminate implementation of the “Step-up” strategy can lead to increased numbers of operations and prolonged hospital stay, as the “Step-up” approach is not appropriate for some patients due to unavailability of a safe puncture path, causing increased trauma to patients [7]. Therefore, we developed and currently apply the “One-step” surgical approach to treat IPN, that is, direct minimally invasive debridement instead of PCD. A preliminary retrospective study data from our center confirmed that “One-step” has better surgical efficacy and safety, but there is a lack of clinical data comparing it with the “Step-up” approach [8]. Consequently, this study is intended to conduct a single-center, randomized controlled trial to compare the “Step-up” with the “One-step” approaches in terms of the composite endpoints which consist of mortality and severe complications to provide a reference for the distribution characteristics of IPN and the selection of minimally invasive surgical procedures. In accordance with the SPIRIT reporting checklist, we present the following article.

## Methods/design

### Study design and setting

This study is a single-center, randomized controlled trial. The research began on May 1, 2021, and is anticipated to end on December 31, 2023. During the research period, patients will be selected from Xuan Wu Hospital, Capital Medical University for treatment. A total of 128 patients will be enrolled in this study. After providing informed consent, enrolled patients will be randomly assigned for surgical treatment to either the experimental group (One-step approach) or the control group (Step-up approach) at a ratio of 1:1 using the block randomization method. Each patient will receive a numeric randomization code. The detailed research process is illustrated in Fig. 1.

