### Secondary outcome

The incidence of organ dysfunction and organ function were evaluated according to the modified Marshall score.Complication: The complication rate mainly includes short-term and long-term complication rates, among which short-term complications include bleeding, gastrointestinal perforation, and pancreatic leakage. Long-term complications include incisional hernia, pancreatic endocrine and exocrine dysfunction, chronic pancreatitis, and portal hypertension. Pancreatic endocrine dysfunction was defined as HbA1c ≥ 6.5% (48 mmol/mol) and/or FPG ≥ 126 mg/dl (7.0 mmol/l) 3 months after diagnosis or pancreatitis. Pancreatic exocrine dysfunction was determined in a variety of ways including direct pancreatic function testing, measurement of fecal elastase or fecal fat levels (72 h fecal fat excretion > 7 g/d) and need for oral pancreatic enzyme replacement therapy. Chronic pancreatitis was defined as repeated upper abdominal pain; abnormal serum or urine pancreatic enzyme concentrations (lipase or amylase activity 2–3 times above the upper limit of normal); abnormal exocrine function (stool elastase < 200 µg/g) while the endosonography/CT/MRI imaging shows dilated main duct and side branches, intraductal and parenchymal calcifications[10, 11].The number of surgical procedures which includes PCD and the total number of operations.Mortality: The incidence of in-hospital death and deaths within 90 days of discharge.The length of hospital stays, the length of intensive care unit (ICU) stay, and hospitalization costs.Changes in inflammatory markers, including white blood cell (WBC), interleukin-6 (IL-6), C-reactive protein (CRP), and procalcitonin (PCT)

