### Follow-up

After the procedure, a full-time staff member will be responsible for the follow-up of the enrolled patients. Each patient will be followed up for two years after discharge by outpatient or inpatient review, telephone, or mail. Patients will be followed up every three months in the first year after surgery and every six months over the second year after surgery. During the follow-up period, patients are required to undergo physical examinations, abdominal CT scans, and laboratory tests. In addition, researchers will monitor for related clinical symptoms, such as abdominal pain, bloating, and fatty diarrhea. Physical examination will be conducted mainly to check for postoperative incisional hernia. Abdominal CT scan will primarily focus on the morphological changes of the pancreas and blood vessels in the abdominal cavity. Laboratory tests will include routine blood tests and blood biochemistry tests, which are concerned with white blood cells, thrombocytes, blood glucose, blood triglycerides, and glycosylated hemoglobin. The detailed follow-up schedule is shown in Table 3.

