### Sample size

The sample size was calculated using PASS 11.0 (NCSS Statistical and Data Analysis, USA) software and was estimated based on the results of our center’s previous research and published literature. According to our previous studies and domestic and foreign reports, the incidence of a mixed endpoint is approximately 20% for the “One-step” approach and approximately 45% for the “Step-up” approach [8]. Using a one-sided test, the α value was equal to 0.05, and the statistical power was 80%. The withdrawal rate was expected to be 20% during the study period. Thus, this study requires at least 128 patients, with 64 patients each group.

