### Trial status

Version 1.0 of the study protocol was approved in December 2020. The trial was registered in March 2021 on the Chinese Clinical Trial Registry website (http://www.chictr.org.cn/index.aspx). We established SOP and CRF for clinical research. Patient enrollment will begin in May 2021 and is anticipated to end in December 2023.

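### The stated end of research and end of enrolment coincide in December 2023, which leaves no room for the two years of follow-up promised to each patient; the follow-up origin is also inconsistent.

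*Protocol article*

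**What the plan says.** Three places give calendar dates, and all of them stop in December 2023.

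- Study design and setting: "The research began on May 1, 2021, and is anticipated to end on December 31, 2023".
- Trial status: "Patient enrollment will begin in May 2021 and is anticipated to end in December 2023".
- Abstract, Methods: "The total sample size required for the trial (May 2021–December 2023) is approximately 128 patients".

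Three places set the length of follow-up.

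- Abstract, Methods: "The patients will be followed up for 2 years after surgery".
- Follow-up: "Each patient will be followed up for two years after discharge by outpatient or inpatient review, telephone, or mail". The next sentence changes the origin: "Patients will be followed up every three months in the first year after surgery and every six months over the second year after surgery".
- Table 3 (Data collection) has follow-up columns at 3, 6, 9, 12, 18 and 24 months.

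The outcomes that need this follow-up are in the Secondary outcome section: "Long-term complications include incisional hernia, pancreatic endocrine and exocrine dysfunction, chronic pancreatitis, and portal hypertension".

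**The concern.** A patient enrolled in late 2023 cannot attend a 24-month visit in research that ends on 31 December 2023. The same is true of anyone enrolled after 31 December 2021. These are explicit statements that conflict, not detail that a journal article leaves to a fuller document.

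At stake are the long-term complications. The Abstract's Background names the missing comparison of long-term as well as short-term efficacy as a reason for the trial. If the database closed on the stated date, that comparison would rest on a minority of patients with complete observation.

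The origin is a second, smaller problem. Surgery and discharge are separated by the postoperative hospital stay, and the Abstract's Discussion expects that stay to be shorter with One-step. The calendar position of the 24-month visit therefore depends on the origin chosen, possibly by a different amount in each arm.

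**Working it through.** **Inputs.** Start 1 May 2021 and end 31 December 2023 (Study design and setting). Enrolment May 2021 to December 2023 (Trial status). Follow-up 24 months (Abstract, Follow-up, Table 3). N = 128, 64 per arm (Sample size). The accrual pattern is not given, so uniform accrual is an assumption, with a range below. Entry date is taken as the date of surgery unless stated otherwise.

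**1. The plan's own figure.** The Sample size section gives 20% versus 45%, one-sided α = 0.05, 80% power and 20% withdrawal. With mean proportion 0.325:

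n = [1.645·√(2·0.325·0.675) + 0.842·√(0.20·0.80 + 0.45·0.55)]² / 0.25² ≈ 42.3, so 43 per arm without continuity correction. The continuity correction raises this to 51. Then 51/(1 − 0.20) = 63.75, so 64 per arm and 128 in total. The stated figure is reproduced. No follow-up time enters this calculation, so the timeline does not affect it.

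**2. Share able to reach each visit by 31 December 2023.** The enrolment window is 245 + 365 + 365 = 975 days, or 32 months. Under uniform accrual, the share reaching m months is the number of days from 1 May 2021 to the last entry date that allows m months, divided by 975.

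| Visit | Last possible entry | Days | Share | Of 128 |
|---|---|---|---|---|
| 24 months | 31 Dec 2021 | 245 | 25.1% | about 32 |
| 18 months | 30 Jun 2022 | 426 | 43.7% | about 56 |
| 12 months | 31 Dec 2022 | 610 | 62.6% | about 80 |
| 9 months | 31 Mar 2023 | 700 | 71.8% | about 92 |
| 6 months | 30 Jun 2023 | 791 | 81.1% | about 104 |
| 3 months | 30 Sep 2023 | 883 | 90.6% | about 116 |

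**3. Mean available follow-up, capped at 24 months.** A quarter of patients could have the full 24 months. The other three quarters would have between 0 and 24, on average 12. So 0.25 × 24 + 0.75 × 12 = 15 months.

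**4. Sensitivity to accrual (24-month share).**

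- Rate rising linearly from zero: (8/32)² = 6.25%, or 8 patients.
- Rate falling linearly to zero: 1 − (24/32)² = 43.75%, or 56 patients.

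**5. Sensitivity to origin.** Suppose follow-up counts from discharge and discharge comes 1 to 3 months after entry (an assumption). The uniform-accrual share is then (8 − 1)/32 = 21.9% down to (8 − 3)/32 = 15.6%, or 28 to 20 patients.

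**6. What would reconcile the dates.**

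- Keep enrolment to December 2023: the last 24-month visit falls in December 2025, or later if counted from discharge.
- Keep 31 December 2023 as the last visit: enrolment must close by 31 December 2021. That needs 128/8 = 16 patients a month, against 128/32 = 4 a month over the stated window.

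**The case against.** The strongest reply is that the dates describe recruitment only. The sentence after the stated end date says that patients are selected from the hospital during the research period, Trial status attaches the same dates to enrolment, and the Abstract attaches them to the required sample size. On this reading follow-up simply continues to about December 2025. This is plausible, and nothing in the article says that follow-up visits stop on 31 December 2023. A reader might infer that the long-term outcomes cannot be delivered; the article does not establish that. The reply does not remove the defect, however. The text says the research ends on that date and gives no later one, so on this reading the end date is mislabelled and still needs correcting.

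A reader might also infer that long-term complications would be compared as crude proportions by chi-square test, so that rates are understated. The Statistical analyses section does not support this. It names chi-square or Fisher's exact test for categorical data and adverse events, but also Kaplan–Meier estimation and a log-rank test for the complication rate. Those methods accommodate administrative censoring, although they cannot supply 24-month observations that were never made.

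Nor should one infer that a common close-out date would bias the comparison between arms. With 1:1 block randomization, calendar entry is roughly balanced, and so is censoring at a fixed date. Counting from discharge could disturb this if hospital stay differs by arm, but the article gives no figures from which to size that.

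**Conclusion.** The timeline is wrong as written: the stated end of research, the stated end of enrolment and 24 months of follow-up for every patient cannot all hold. Whether follow-up will really be cut short, or only the end date is misstated, cannot be settled from the article.

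The 25% and 15-month figures apply only if data close on the stated date and accrual is uniform. Under each accrual pattern tried, a majority of patients would miss the 24-month visit. The consequence is confined to the long-term secondary complications. The article gives no assessment window for the primary composite that would tie it to the 24-month visits.

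**What to change.** - In the Abstract, Study design and setting, and Trial status, give two dates: the end of enrolment (December 2023), and the last 24-month visit and study end (no earlier than December 2025, later if counted from discharge).
- Choose one origin for the 24 months, surgery or discharge, and use it in the Abstract and throughout the Follow-up section.
- If any long-term results are to be reported before all patients reach 24 months, state that they will be analysed with the time-to-event methods already named in Statistical analyses, with administrative censoring, not as simple proportions.

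The cost is an amendment of dates and wording. The visits are already promised in Table 3, so no new assessments are added. The downside is that complete long-term results come about two years after the currently stated end.

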**Fig. 1 Fig1:**
[figure not shown]
Research process flow chart

### Ethics approval and informed consent

This study has been approved by the Ethics Committee of Xuan Wu Hospital, Capital Medical University. The ethical approval number is 2020-052. According to the requirements of the Ethics Committee, clinical research will be conducted only after the enrolled patients have signed informed consent forms. This study was designed in accordance with the principles of the Declaration of Helsinki (as revised in 2013). All data will be recorded and analyzed anonymously to protect patient privacy. The trial was registered in March 2021 on the Chinese Clinical Trial Registry website (http://www.chictr.org.cn/index.aspx); registration number ChiCTR2100044348. Participating patients will be informed of the purpose and significance of the study, the benefits and possible risks of participation, and the confidentiality of the study.

### Inclusion criteria

The patient was diagnosed with acute pancreatitis with infected pancreatic necrosis by abdominal computed tomography (CT) scan and laboratory examination, (e.g. CT scan showed “bubble” sign or bacteria or fungi are detected by fine-needle aspiration and culture).Infected pancreatic necrosis mainly included acute necrotic collection with infection, walled-off necrosis with infection, and isolated infected peri-pancreatic necrosis.Patients are between 18 and 80 years old, regardless of sex.The patient’s general condition is stable without multiple organ failure (according to the modified Marshall score).The patient was not treated with PCD or the target infected area was not treated with PCD.The patient was qualified for video-assisted minimally invasive debridement and signed the informed consent for treatment.The patient is capable of following the study protocol and follow-up scheme.

### Exclusion criteria

Previous history of pancreatic necrotic tissue drainage or debridementPrevious exploratory laparotomy for acute abdominal disease or pancreatitisThe patient experienced acute exacerbation of chronic pancreatitisPatients with acute pancreatitis with abdominal compartment syndrome or abdominal organ perforationPatients with acute pancreatitis due to abdominal surgeryPatients who cannot tolerate video-assisted minimally invasive debridement and anesthesia due to physical conditionPatients participate in other clinical studies.

### Elimination criteria

The patient cannot comply with randomization.The patient’s clinical data were incomplete and could not be statistically analyzed.Researchers eliminated enrolled patients from study for patient’s benefit.The patients violated the study protocol and received other therapies during the study period.

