### Primary outcome

The primary outcome is the composite endpoint, which consists of mortality and severe complications (Clavien-Dindo ≥ IIIa). According to the Clavien-Dindo classification, postoperative complications classified as higher than Grade IIIa will be regarded as clinically significant (Table 1) [9].

**Table 1 Tab1:** Clavien-Dindo Classification

Grade	Definition
I	Any complication that deviates from the natural course after surgery, including the use of antiemetics, antipyretics, analgesics, diuretics, infusion, and physical therapy, as well as bedside debridement of incision infection
II	Medications other than those permitted for grade I complications are required, including blood transfusion and total parenteral nutrition support
*III*	Surgical, endoscopic, and radiotherapy are required
IIIa	No general anesthesia is required
IIIb	Need for general anesthesia
*IV*	Life-threatening complication, including centeral nervous system complications and required intermittent monitoring or intensive care unit (ICU) treatment
IVa	Single organ dysfunction
IVb	Multi-organ dysfunction
V	Death

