### Statistical analyses

The results of this trial for primary outcomes will be analyzed based on both the intention-to-treat protocol and per-protocol datasets. SAS 9.2 software (SAS Institute Inc.) was used to generate the randomization sequence. Statistical analyses will be performed with SPSS 21.0 (IBM Corp., Armonk, NY, USA) statistical software. The continuous variables with normal distributions will be described as mean ± standard deviation, and an independent sample *t-test* will be used for difference tests. The continuous variables with non-normal distributions will be described by the median (IQR), and the Mann–Whitney U test will be used for the difference tests. The Chi-square test or Fisher’s exact test will be used for categorical data. The Chi-square test or Fisher’s exact test will be used to assess adverse events. The Kaplan–Meier method will be used to calculate survival analysis. The log-rank test will be used to compare the complication rate between the two groups, and *P* values < 0.05 will be considered statistically significant.

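### The elimination criteria take enrolled patients out of the study without being limited to the per-protocol set, which conflicts with the promised intention-to-treat analysis

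*Protocol article*

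**What the plan says.** The protocol article has an Elimination criteria section, separate from the inclusion and exclusion criteria. It gives four reasons:

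- "The patient cannot comply with randomization";
- the patient's "clinical data were incomplete and could not be statistically analyzed";
- "Researchers eliminated enrolled patients from study", on the ground of the patient's benefit;
- "The patients violated the study protocol and received other therapies during the study period".

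The section names no analysis set.

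Under Statistical analyses, the primary outcome "will be analyzed based on both the intention-to-treat protocol and per-protocol datasets". Neither dataset is defined there, and the sentence does not refer back to the elimination criteria. On the endpoint, "The primary outcome is the composite endpoint, which consists of mortality and severe complications", the latter from Clavien-Dindo grade IIIa upward. The Sample size section adds: "The withdrawal rate was expected to be 20% during the study period".

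Three other places bear on the point. The blinding section says that surgeons treat according to the known allocation. The Background and Discussion say that some patients lack a safe puncture path for percutaneous drainage (PCD). The Follow-up section provides two years of follow-up for each patient and makes no exception for eliminated patients.

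**The concern.** An intention-to-treat analysis keeps every randomised patient in the arm assigned. A rule that removes patients from the study for not following the allocation, for incomplete data or for departing from protocol treatment cannot operate alongside it unless the rule is confined to another analysis set.

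Removal could depend on arm. Step-up starts with PCD and One-step does not. The inclusion criteria require suitability for video-assisted debridement but not a safe route for PCD. A patient without such a route could therefore be unable to comply if allocated to Step-up, yet fully able if allocated to One-step. Removal for the patient's benefit has no stated criteria in the article, and the surgeons are unblinded.

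Removal could also depend on outcome. Table 1 defines grade III by treatment need ("Surgical, endoscopic, and radiotherapy are required"), so a complication that leads to a further procedure can itself be a primary event. If that procedure were also classed as a protocol violation with other therapy, the same episode would create the event and remove the patient. At stake is the primary comparison, and the interim look at the primary endpoint planned at 64 patients.

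**Working it through.** **1. The texts side by side.** One elimination reason speaks of removal from the study, and another of data that cannot be analysed statistically. The analysis section promises intention-to-treat and per-protocol results. The texts are compatible only if elimination affects the per-protocol set alone, and the article does not say that.

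**2. The plan's own figure.** Inputs from the Sample size section: 20% versus 45%, one-sided α = 0.05, power 80%, withdrawal 20%.

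- Uncorrected n per arm = [1.645·√(2·0.325·0.675) + 0.842·√(0.20·0.80 + 0.45·0.55)]² / 0.25² = 42.3, rounded up to 43.
- With continuity correction: 51 per arm.
- With withdrawal: 51/(1 − 0.20) = 63.75, so 64 per arm and 128 in total.

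The stated 128 reproduces exactly, so this point does not rest on an arithmetic error. The design allows for losing 64 − 51 = 13 patients per arm. That is a planning allowance for withdrawal, not an elimination rate, and it is not specific to either arm.

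**3. How far removal can move an observed rate.** If a fraction f of an arm with true event rate p is removed, and the removed patients have event rate r, the remaining patients show

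observed rate = (p − f·r)/(1 − f).

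Assumptions for illustration: no true effect, with p = 32.5% in both arms (the midpoint of 20% and 45%); f = 20% in one arm and none in the other. The values of r are assumed and appear nowhere in the documents.

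| r | Calculation | Observed rate | Shift (points) |
|---|---|---|---|
| 20% | (0.325 − 0.040)/0.8 | 35.6% | +3.1 |
| 32.5% | (0.325 − 0.065)/0.8 | 32.5% | 0 |
| 50% | (0.325 − 0.100)/0.8 | 28.1% | −4.4 |
| 60% | (0.325 − 0.120)/0.8 | 25.6% | −6.9 |
| 80% | (0.325 − 0.160)/0.8 | 20.6% | −11.9 |

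The planned difference is 25 points. If both arms lose 20% with r = 60%, both read 25.6%: the difference is zero under the null, although both rates are understated.

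**4. Effect on the test.** A simulation on different assumed inputs: both arms truly at 45%, 64 per arm, one-sided 5% test, a share q of One-step failures eliminated and no Step-up patients.

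| q | Mean number removed | Apparent One-step rate | One-sided type I error |
|---|---|---|---|
| 0 | 0 | 45.0% | 4.6% |
| 10% | 2.9 | 42.4% | 8.9% |
| 20% | 5.8 | 39.6% | 15.1% |
| 30% | 8.6 | 36.4% | 24.6% |
| 44% | 12.7 | 31.4% | 44.3% |

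Selective removal of about three failures from one arm roughly doubles the error rate. Removing Step-up failures instead would push the comparison the other way.

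**The case against.** The strongest reply is that the section simply defines who leaves the per-protocol set. A plan with a per-protocol analysis needs such criteria, this is the only text that could supply them, and nothing in it says that eliminated patients leave the intention-to-treat set. On that reading the conflict disappears. This stands as a possible reading, but the text does not state it, and its reference to removal from the study points the other way.

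Four further points have weight:

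- The fourth criterion requires a protocol violation as well as other therapy. Surgery after failed PCD, further PCD for residual infection and open surgery as a last measure all belong to the described Step-up pathway. A reader might infer that every patient who fails and is rescued would be eliminated; the documents do not support that.
- Enrolment precedes randomisation in the study design section, so some eliminations could happen before or at allocation. The fourth criterion, at least, describes events after treatment has begun.
- Follow-up covers each patient, and serious adverse events are recorded from consent to the end of the trial. Outcomes of eliminated patients may therefore be collected. That makes the fix easier but does not say in which analysis those outcomes count.
- The handling of missing data and the order of precedence between the two datasets are ordinary analysis-plan content. Their absence from the article is not a fault and is not counted as one here.

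The analysis plan could define the analysis sets. It could not recover outcomes that were never collected because removal from the study had been taken literally.

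**Conclusion.** The point holds in this form: the protocol states a removal rule that is not confined to the per-protocol set, and applied as written it is incompatible with its own intention-to-treat commitment. It permits exclusion related to arm and outcome.

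The size and direction of the bias are unknown. The fall from 32.5% to 25.6% is an illustration that assumes 20% elimination in one arm only and a 60% event rate among those eliminated. Elimination at the same rate and with the same event rate in both arms gives no spurious difference under the null.

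A reader might go further and conclude that the result labelled intention-to-treat will in fact be per-protocol, or that a spurious benefit of 7 to 12 points is to be expected. The documents do not support either conclusion. The per-protocol reading remains open, and no document gives an elimination rate, its split between arms or the event rate among those eliminated.

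**What to change.** - State in the Elimination criteria section that the four reasons define exclusion from the per-protocol set only.
- State under Statistical analyses that the intention-to-treat set contains every randomised patient in the assigned arm, whatever treatment was received, and that all of them stay in the planned follow-up for death and complications.
- In the same sentence, name intention-to-treat as the primary analysis and per-protocol as supportive.
- Add a sensitivity analysis for patients whose composite status is missing.

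The cost is protocol wording; the follow-up schedule already exists and N stays at 128. If all 64 per arm are analysed, one-sided power at 20% versus 45% is 92.3% by the uncorrected formula, against 86.2% with 51 per arm. That gain assumes no dilution. The downside is that patients who leave their assigned strategy may dilute the treatment contrast somewhat, which the supportive per-protocol analysis can help to describe.
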